# A randomized double-blind placebo-controlled multicenter trial of Bushen Yisui and Ziyin Jiangzhuo formula for constipation in Parkinson disease

**DOI:** 10.1097/MD.0000000000021145

**Published:** 2020-07-10

**Keywords:** complementary therapy, constipation, Parkinson disease, traditional Chinese medicine

## Abstract

**Introduction::**

Constipation is a common nonmotor symptom of Parkinson disease (PD). Constipation can also impact patient's quality of life. Chinese herbal medicines have been used for the treatment of constipation in PD. This trial will evaluate the efficacy and safety of a Chinese herbal formula Bushen Yisui and Ziyin Jiangzhuo (BYZJ) for the treatment of constipation in PD.

**Methods and analysis::**

This randomized, double-blind, placebo-controlled, multicenter clinical trial will involve 4 hospitals in Beijing, China. The study will aim to recruit 90 PD patients with constipation between 30 and 80 years-of age with a score of 1 – 4 on the Hoehn and Yahr scale. Once recruited, Patients will be randomized into a BYZJ group or a placebo group in a 2:1 ratio. The trial will include a 1-week run-in period, a 4-week double-blind treatment period, a 4-week and a 12-week follow-up period. All patients will be educated about PD-related constipation during the run-in period. BYZJ granules and simulated granules will be administered twice daily for 4 weeks to the BYZJ group and the placebo group respectively. Assessments will be performed during run-in period, before the start of treatment (baseline, week 0), and at 4, 8, and 16 weeks. The primary outcome will be measured with the Constipation Severity Instrument, and secondary outcomes will be evaluated with the Patient Assessment of Constipation Quality of Life questionnaire, Bristol Stool Form Scale, Movement Disorders–Unified Parkinson Disease Rating Scale, Nonmotor Symptoms Scale, PD Sleep Scale, Parkinson Fatigue Scale-16. Laxative use (dose and frequency) will also be recorded. Intention-to-treat and per-protocol set analyses will be used to compare symptom improvement between the 2 groups. Any adverse events will be recorded.

**Discussion::**

If found effective and safe, BYZJ formula will be one of Chinese herb to treat constipation and even other nonmotor or motor symptoms in PD patients. The results will sustain the broader use of BYZJ formula in PD.

## Introduction

1

Constipation is a common non-motor symptom (NMS) of Parkinson disease (PD).^[1,2]^ In China, 64.7% of PD patients experience constipation,^[3]^ and 47.8% use laxatives,^[4]^ which reduces their quality of life. Long-term use of laxatives—especially of the irritant type—can lead to dependence and intestinal dysfunction, which aggravates constipation. A variety of medications for the treatment of PD can cause constipation such as levodopa; conversely, constipation affects intestinal absorption of levodopa, thereby reducing its efficacy and aggravating PD symptoms.^[5]^

Chinese herbal medicines have long been used to treat PD. In recent years, traditional Chinese medicine (TCM) has focused more attention on the treatment of PD-related constipation, with many reports demonstrating that it can be alleviated by certain preparations.^[6,7]^ However, there is a dearth of high-quality clinical studies on this subject.^[8]^

The Chinese herbal formulation Bushen Yisui and Ziyin Jiangzhuo (BYZJ) was developed based on practical experiences from TCM, It is used to regulate bowel movements and alleviate insomnia, fatigue, and anxiety, among other conditions. According to the dialectic principles underlying TCM, constipation in PD is caused by a deficiency in kidney and marrow essence (ie, Qi and Yin).^[7–9]^ Thus, strengthening Qi and Yin and nourishing the kidney and marrow is a potential treatment strategy.

The objective of the present study is to assess the efficacy and safety of BYZJ in the treatment of constipation and other NMS as well as motor symptoms (MS) in PD patients.

## Methods/design

2

This protocol is reported in accordance with the Standard Protocol Items: Recommendations for Interventional Trials guidelines.^[10]^

## Hypothesis

3

BYZJ is effective and safe for the treatment of constipation, along with other NMS and MS, in patients with PD.

## Study design

4

This will be a randomized, double-blind, and placebo-controlled multicenter trial. We aim to recruit 90 patients who will be assigned by stratified randomization (in a 2:1 ratio) to intervention (BYZJ) and control (placebo) groups. The total study duration will be 9 weeks, with a 1-week run-in period, an intervention time of 4 weeks, and 4-week and 12-week washout follow-up periods. Efficacy and safety will be assessed at baseline (week 0) and at 4, 8, and 16 weeks (Fig. 1).

**Figure 1 F1:**
[figure not shown]
Study design flow chart. The 17-wk study will include a 1-wk run-in period, an intervention time of 4 wk, 4-wk, and 12-wk washout follow-up. Efficacy will be assessed at baseline (week 0) and at 4, 8,16 wk and safety will be assessed at baseline (week 0) and at 4, 16 wk.

## Recruitment, study setting, and participants

5

Participants will be recruited from the PD outpatient clinic of Beijing Rehabilitation Hospital, Capital Medical University, Xiyuan Hospital of China Academy of Chinese Medical Sciences, Dongzhimen Hospital of Beijing University of Chinese Medicine, and Beijing Longfu Hospital. We will also aim to recruit patients through announcements in the media and advertisements that will be published on official information platforms and the bulletin boards of each study site. Interested prospective subjects will be able to contact investigators using the telephone numbers provided. An investigator will conduct a face-to-face interview with each respondent to explain the study. Those who volunteer to participate will be required to sign appropriate consent forms.

## Inclusion and exclusion criteria

6

To be included in the trial, participants must meet the following criteria: diagnosed with idiopathic PD according to the 2015 Movement Disorder Society criteria^[11]^; diagnosed with constipation according to the Rome III criteria^[12]^; between 30 and 80 years-of-age; have symptoms that are classified as scale 1 to 4 according to the Hoehn and Yahr scale; provide informed consent and confirm that they will be able to complete the whole treatment; and refrain from participating in other clinical trials during the study and follow-up period. The exclusion criteria are as follows: patients who do not take their medication under the guidance of a doctor or cannot take their medication regularly; patients with Parkinsonism-Plus syndrome or Secondary Parkinson syndrome caused by drugs, metabolic diseases, encephalitis, stroke, brain tumours, carbon monoxide poisoning, and other neurologic degenerative diseases; patients with organic intestinal lesions such as intestinal polyps, intestinal tuberculosis, Crohn disease, tumours, and ulcers; patients with secondary constipation caused by uremia, muscular dystrophy, multiple sclerosis, hypothyroidism and other system diseases; patients with severe heart, brain, liver, kidney, and blood diseases, as well as mental disorders or dementia; patients with serum creatinine, alanine aminotransferase, or aspartate transaminase levels more than twice the normal value; according to the investigators’ judgment, patients who are unable to cooperate throughout the study because of drug abuse or poor adherence (as judged by the investigators); patients who participated in other studies in the previous 2 weeks or are currently participating in other clinical trials, or have taken other TCM preparations in the previous 3 months; pregnant and lactating women; and patients or family members who are unwilling to cooperate or do not agree to sign the informed consent form.

## Sample size

7

The minimum sample size for statistical significance with a 2-sample 1-sided *t* test was estimated based on the results of a previous study involving the treatment of patients with PD-related constipation.^[13]^ Based on a 2:1 ratio of patients in the BYZJ and placebo groups, the minimum sample size was calculated with formula shown in Eq. (1).: 

In Equation 1, n represents the sample size of each group, κ = nA/nB; μ represents the overall mean, μA represents the mean of group A, μB represents the mean of group B; σ represents the overall standard deviation, σA represents the standard deviation of group A, σB represents the standard deviation of group B; α represents type 1 errors; and β represents type 2 errors. Application of Eq. (1) showed that 52 are required for the BYZJ group and 26 cases are required for the placebo group. Considering a 15% dropout rate, we plan to recruit 60 and 30 cases for the BYZJ and placebo groups, respectively.

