## Statistical analysis

16

SPSS v20.0 software (SPSS Inc., Chicago, IL) will be used for all data processing and analysis. Measurement data will be expressed as mean ± standard deviation. The normality and homogeneity of variance will be tested. Data with a normal distribution and uniform variance will be evaluated with the independent samples *t*-test for between-group comparisons. Data that do not meet these criteria will be evaluated with a nonparametric test. Repeated measures analysis of variance will be used for within-group comparisons (1-way analysis of variance will be used if the data meet the Huynh–Feldt condition; otherwise, a mixed model will be used).

Numerical (count) data will be expressed as percentages. Between-group comparisons will be performed with the *χ*^2^ test. Intent-to-treat and compliance analyses will be performed to compare efficacy between the 2 groups. The last observation carry-forward method will be used for data processing. The significance level for each test will be set at *P* < .05.

An intention-to-treat analysis will be adopted to deal with missing data, including all participants in the analysis based on the initial group allocation. A linear mixed model approach (a direct likelihood estimation method) will be applied to analyze all continuous variables as value is missing at random.

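### The minimum of 52 + 26 is derived for a one-sided t test, but the analysis section tests at P < .05 and names no one-sided test, so sizing and analysis do not match as written

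*Protocol article*

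**What the plan says.** Section 7 (Sample size) describes its result as "The minimum sample size for statistical significance with a 2-sample 1-sided" t test, based on an earlier study in PD-related constipation and a 2:1 allocation. It reports that "52 are required for the BYZJ group and 26 cases are required for the placebo group", and then: "Considering a 15% dropout rate, we plan to recruit 60 and 30 cases for the BYZJ and placebo groups, respectively". The inputs appear only as symbols: "α represents type 1 errors; and β represents type 2 errors", and likewise "μA represents the mean of group A, μB represents the mean of group B" and "σA represents the standard deviation of group A, σB represents the standard deviation of group B". The text attaches no number to any of them.

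Section 16 (Statistical analysis) says "The significance level for each test will be set at" P < .05. For between-group comparison of continuous data it names the independent-samples t test, with a nonparametric test if assumptions fail, and it also applies a linear mixed model to continuous variables. Count data get a chi-square test, and within-group comparisons get repeated measures ANOVA. No side is given for any of these. Section 12 makes the change in CSI score the primary outcome. Section 3 words the hypothesis directionally (BYZJ is effective) but fixes no test side.

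**The concern.** A sample size is the minimum only for the test it was computed for. Section 7 commits to one side. Section 16 uses an unqualified P < .05, which most readers, and the default output of most software, take as two-sided. With one-sided 5% sizing there are two possibilities:

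- **The analysis is two-sided.** Then 52 + 26 gives less power than was planned, and a null result could be misread as coming from an adequately powered trial.
- **The analysis is one-sided at .05.** Then benefit can be declared on weaker evidence than P < .05 normally conveys, and section 16 does not say so.

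Leaving the side open also allows it to be settled after the data are seen. All of this bears on the primary efficacy comparison.

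**Working it through.** **Inputs from the article.** One-sided two-sample t test, 2:1 allocation, 52 + 26 evaluable, 15% dropout, 60 + 30 recruited (section 7); P < .05 with no side stated (section 16).

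**Inputs not in the text.** Sizing alpha, power, difference and SD. The 52 + 26 therefore cannot be reproduced. Equation (1) could not be read in the copy used here, and nothing is held against the plan for that. The check back-solves the standardised difference d that 52/26 implies under assumed alpha and power, then evaluates the same d two-sided.

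**Step 1: implied effect, one-sided alpha .05 assumed.**

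d = (z(1−α) + z(power)) × √(1/26 + 1/52), where √(1/26 + 1/52) = 0.2402.

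For 80% power: d = (1.645 + 0.842) × 0.2402 = 0.597.

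**Step 2: two-sided .05 power at 52/26 for that d.**

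Power = Φ(d/0.2402 − 1.960). For planned 80%: Φ(2.486 − 1.960) = 0.701.

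| Planned power (one-sided .05) | Implied d | Two-sided power, normal | Two-sided power, noncentral t (76 df, d re-solved) |
|---|---|---|---|
| 80% | 0.597 | 0.7007 | 0.6975 |
| 85% | 0.644 | 0.7646 | 0.7615 |
| 90% | 0.703 | 0.8331 | 0.8303 |
| 95% | 0.790 | 0.9082 | 0.9061 |

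**Step 3: sizing at one-sided .025 instead.** The critical value is 1.960 in both calculations, so two-sided .05 power equals planned power and 52 + 26 stands.

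**Step 4: detectable effect with 80% power at 52/26.** One-sided .05: 0.597 SD (normal) or 0.603 SD (t). Two-sided .05: (1.960 + 0.842) × 0.2402 = 0.673 SD (normal) or 0.682 SD (t).

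**Step 5: all 60 + 30 analysed, 80% case.** √(1/30 + 1/60) = 0.2236; Φ(0.5972/0.2236 − 1.960) = 0.761.

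**Step 6: size that would restore 80% two-sided in the 80% case.** n(placebo) = 1.5 × ((1.960 + 0.842)/0.597)² ≈ 33.01, which rounds up to 34. That is 68 + 34 = 102 evaluable, shown for scale only.

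**Step 7: false-benefit rate.** A one-sided .05 test puts 5% in the direction of benefit; a two-sided .05 test puts .05/2 = 2.5% there.

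**The case against.** The strongest reply is that section 16 is silent on side rather than contradictory. A t test, a rank test or a mixed-model contrast can all be run one-sided, and the hypothesis is directional. Chi-square and ANOVA are inherently non-directional, but they are assigned to count data and within-group comparisons, so they do not settle the side of the primary comparison. A full protocol or analysis plan may state it. This stands in part: the article does not prove that the primary test will be two-sided. It does not remove the point, because the article itself gives a side for sizing and then an unqualified P < .05 for analysis, which a reader will take as two-sided.

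A reader might infer that a trial planned for 80% power has only 70%. The documents do not support that. No planned power is stated, 70% is one point in a range from 70% to 91%, and one-sided .025 sizing, which the text does not exclude, involves no loss. Nor can one infer that 52 + 26 was miscalculated, since the inputs needed to check it are not in the text.

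It is also fair that section 16 plans an intention-to-treat analysis. If all 60 + 30 contribute, the 80% case gives about 76% rather than 70%. That narrows the gap without closing it. One might add that baseline adjustment would make up the rest, but no baseline-to-follow-up correlation is given, so this cannot be relied on.

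Finally, one-sided .05 is disclosed in section 7 as to side, though not as to level, and preferring one-sided .025 is a convention the article does not set. Even so, the side would have to appear in section 16 for readers to know which error rate applies.

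**Conclusion.** The point holds in conditional form: the sizing rule and the analysis rule for the primary comparison do not match as written. The missing input values are not themselves the defect, but they prevent a reader from telling how much the mismatch matters.

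If sizing used one-sided .05, two-sided power at 52/26 falls short of plan by about 10 percentage points at a planned 80% (80% to 70%) and by about 4 at a planned 95% (95% to 91%). If the analysis is one-sided at .05, power is as planned but the false-benefit rate is twice that of a two-sided 5% test. If sizing used one-sided .025, only the wording needs correcting. The power figures assume a two-group comparison of means with a common SD; they are not power for the linear mixed model.

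**What to change.** Before unblinding, state in both section 7 and section 16 that the primary test of CSI change is two-sided at .05 (equivalently one-sided .025). In section 7, print the alpha, beta, difference and SD used, and restate what 52/26 evaluable patients give on that basis: either the power for the planning difference or the detectable difference (about 0.67 to 0.68 SD with 80% power). If the original alpha was one-sided .025, say so; the figures then stand.

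The cost is a rewritten sample-size paragraph and a sentence in section 16. No added patients and no change in trial conduct are required. The only downside is that, if sizing was at one-sided .05, the stated power becomes less favourable.

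### Recruiting 60 and 30 covers about 13% dropout, not the stated 15%: a 15% loss leaves 51 and 25.5 patients, just under the protocol's own minimum of 52 and 26 (minor)

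*Protocol article*

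**What the plan says.** The Sample size section derives its numbers from a two-sample, one-sided t test with 2:1 allocation and describes the result as a minimum: "The minimum sample size for statistical significance with a 2-sample 1-sided *t* test was estimated based on the results of a previous study". It reports that "52 are required for the BYZJ group and 26 cases are required for the placebo group". The next sentence adds the allowance for loss: "Considering a 15% dropout rate, we plan to recruit 60 and 30 cases for the BYZJ and placebo groups, respectively". The abstract repeats the total ("The study will aim to recruit 90 PD patients with constipation"), and the Study design section gives the same 90 at 2:1.

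The step from 52 and 26 to 60 and 30 is not written out. The symbols of the sample-size formula are defined, but the text gives no values for the means, the standard deviations, alpha or beta; for the last two it says only "α represents type 1 errors; and β represents type 2 errors".

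The Statistical analysis section plans an intention-to-treat analysis of everyone as allocated, using last observation carried forward and a likelihood-based linear mixed model, together with a compliance analysis. The abstract calls the latter a per-protocol set analysis.

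**The concern.** A dropout allowance is meant to ensure that, after the expected fraction is lost, the required number remains. If N patients are recruited and a fraction d is lost, N × (1 − d) remain, so N must be at least n / (1 − d). Multiplying n by (1 + d) always falls short, because (1 + d)(1 − d) = 1 − d², which is below 1.

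Here the required numbers, the dropout rate and the recruitment target stand in consecutive sentences, so they can be checked against each other without any outside input. If they disagree, a reader is told that the trial can lose 15% of its patients and still meet its minimum when it cannot. The target contains no reserve beyond this allowance that would absorb the difference.

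**Working it through.** **Inputs** (all from the Sample size section of the protocol article): minimum n of 52 BYZJ and 26 placebo, total 78; dropout d = 15%; planned recruitment 60 and 30, total 90.

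**1. Reproducing the planned figures.** n × (1 + d):
- BYZJ: 52 × 1.15 = 59.8, rounded up to 60.
- Placebo: 26 × 1.15 = 29.9, rounded up to 30.

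Both planned numbers are matched.

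**2. What remains after a 15% loss.** N × (1 − d):
- BYZJ: 60 × 0.85 = 51.0, which is 1 below 52.
- Placebo: 30 × 0.85 = 25.5, which is 0.5 below 26. In whole patients this is 25 or 26, so the placebo shortfall is 0.5 on expectation and 1 if rounded down.
- Total: 76.5 against 78.

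**3. Recruitment that would cover 15%.** n / (1 − d):
- BYZJ: 52 / 0.85 = 61.18, so 62.
- Placebo: 26 / 0.85 = 30.59, so 31.
- Total: 93, still exactly 2:1. Inflating only the total gives 78 / 0.85 = 91.8, so 92.

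**4. Dropout that 60 and 30 do cover.** 1 − n / N: 1 − 52/60 = 1 − 26/30 = 13.3% in each arm.

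**5. Effect on power.** The text gives no alpha, power or effect size, so the following are assumptions, shown as a range. Suppose 52/26 was chosen to give exactly 80% or 90% power at one-sided alpha 0.05 or 0.025. By the normal approximation, the implied standardised difference is δ = (z for 1 − alpha + z for power) × √(1/52 + 1/26), and power at other sizes is Φ(δ / √(1/nA + 1/nB) − z for 1 − alpha).

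| One-sided alpha | Assumed power at 52/26 | Implied δ (SD) | Power at 51/25.5 | Power at 51/25 |
|---|---|---|---|---|
| 0.05 | 80% | 0.597 | 79.32% | 78.85% |
| 0.05 | 90% | 0.703 | 89.49% | 89.14% |
| 0.025 | 80% | 0.673 | 79.23% | 78.71% |
| 0.025 | 90% | 0.779 | 89.44% | 89.05% |

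The loss is 0.5 to 0.8 percentage points at 51/25.5 and 0.9 to 1.3 at 51/25. A two-sided test at 0.05 gives the same figures as the one-sided 0.025 rows.

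**The case against.** The strongest reply is that the shortfall has almost no practical weight. It is 1 of 52 patients in one arm and 0.5 to 1 of 26 in the other, and the 15% is itself a planning guess. That stands, and it is why the point is minor.

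A second reply is that the intention-to-treat analysis keeps all 90 randomised patients, so dropouts are not removed and 51 and 25.5 describe completers, as in the compliance analysis. This limits the consequence but does not make the sentence true. By making a dropout allowance at all, the Sample size section treats dropouts as lost to the required 52 and 26. Keeping a patient in the analysis set also does not restore the missing data. The Outcome measures and safety section schedules the primary outcome at week 0 and then only at weeks 4, 8 and 16. Someone who leaves before week 4 has no later score, so carrying forward repeats the baseline value and the mixed model gains no post-baseline information.

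A third reply is that the article shows no inflation formula. That also stands. Multiplication by 1.15 is inferred from the match in step 1 and is not documented. The point does not depend on it: however 60 and 30 were reached, a 15% loss leaves fewer than 52 and 26.

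A reader might go further and infer that the trial is underpowered, or that 90 patients are too few. The documents do not support this. Without values for alpha, beta, means or standard deviations, neither the 52/26 nor any single power figure can be recomputed, and over the range of assumptions above the loss is at most about 1.3 points.

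**Conclusion.** Wrong as written, and minor. At the protocol's own dropout rate, its own recruitment target misses its own minimum in both arms: 51 against 52 and 25.5 against 26. The target covers 13.3% dropout rather than 15%. This part takes 52 and 26 as given and needs no assumption beyond equal dropout in both arms, which the single stated rate implies. The power loss of roughly 0.5 to 1.3 percentage points does rest on assumed values of alpha and power. The finding is a misstated retention margin. It does not threaten the trial's design, analysis or interpretation.

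**What to change.** Either of two changes to the Sample size section is enough, and both keep 90 patients:

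- State that recruiting 60 and 30 allows for about 13% dropout (1 − 52/60 = 1 − 26/30 = 13.3%).
- Keep the 15% rate, state that it leaves about 51 BYZJ and 25 to 26 placebo completers, and give the power for those numbers from the sponsor's own alpha, effect size and standard deviation.

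Each costs one sentence and no additional patients; the second also needs one power calculation from inputs the sponsor already holds. If the sponsor prefers to keep the full 15% allowance with 52 and 26 remaining, the target becomes 62 and 31, which is three more patients, and the total of 90 in the abstract and the Study design section must change with it. The size of the shortfall does not make that necessary.
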